## **eAppendix 1: Protocol:**

### **1.1 Protocol summary**

Atrial fibrillation (AF) is the most common cardiac arrhythmia globally. Patient knowledge of AF and approaches to medical therapy for AF is poor. This study aims to test the utility and scalability of an AF educational program developed by staff at Westmead Hospital.

#### **Hypothesis:**

Patients exposed clinician-developed educational videos prior to and post clinic appointment will higher knowledge of AF, medication adherence and satisfaction with clinical care compared to usual care.

#### **Primary Objective:**

**The primary objective of this study is to assess whether simple, clinician designed educational program can improve knowledge of AF at 90 day follow up compared to usual care.**

#### **Design**

Randomised clinical trial amongst 200 patients accessing clinical care for atrial fibrillation within Westmead Hospital. Randomisation to intervention and control will be in a 1:1 ratio. Intervention participants (n = 100) will receive a series of 4 clinician-developed educational videos on atrial fibrillation. Control (n = 100) will receive usual care.

#### **Specific Aims:**

**To examine, among patients with atrial fibrillation accessing clinical care whether a series of clinician-designed educational videos delivered prior to clinic improves:**

1. Knowledge of AF
2. Adherence to AF-related medication
3. Satisfaction with clinical care

## 2. Background:

Atrial fibrillation (AF) is the most common cardiac arrhythmia globally and its prevalence is expected to double by 2050. Patients with AF have an approximately 5-fold increased risk of stroke compared to the general population. Appropriate anticoagulation has been demonstrated to significantly reduce the risk of stroke and mortality in patients with AF. Yet, the decision to anti-coagulate is complex and must be balanced against multiple individual patient factors, especially the concomitant risk of bleeding.

In recognition of the multifaceted and complex nature of AF management, the updated 2018 National Heart Foundation guidelines for the management of AF make a strong recommendation for the use of shared decision making as well as ‘targeted patient education throughout the continuum of AF management’. However, the development and implementation of targeted education can be costly and time consuming for both physicians and patients. Due to this, there are limited local AF educational resources available that are appropriate for the patient population at Westmead Hospital.

To address this shortfall, we have developed a series of simple educational videos on AF that cover what AF is, its diagnosis and management. The intervention has been evaluated in an observational, non-randomised study of 104 patients with AF. 96.4% of participants were ‘very satisfied’ with the videos (5 on 5-point Likert scale). Videos were also rated highly on their potential for reducing peri consultation anxiety (median = 90%), improving decision making ability (median = 90%) and likelihood of following treatment plans (median = 93%). However, we have limited data describing the impact of this intervention on patient understanding of AF, adherence to AF-related treatments and overall satisfaction with clinical experience. Whilst studies have been performed that evaluate the potential for educational interventions to impact AF knowledge and treatment adherence, we are not aware of any studies that have compared the efficacy of low and high cost educational interventions in the same patient population.

**Aim and Objectives:** To evaluate the acceptability and utility of a simple clinician designed educational intervention for patients with AF compared to usual care. Specifically, to describe the impact of the intervention on:

- Knowledge of AF at 90 day follow up
- Medication adherence at 90 day follow up
- Satisfaction with clinical care
- Motivation to maintain adherence to AF medication post intervention delivery and at 90 day follow up

### 3. Research Plan and Methods:

#### 3.1 Experimental design:

[figure not shown]

eFigure 1: Participant flow

#### Overall Study

This is a randomised controlled trial (RCT) of 200 patients who are accessing clinical care at Westmead hospital. Individuals will be randomised in a ratio of 1:1 (intervention : control). Randomisation will occur centrally prior to study implementation to intervention (educational videos) or control (usual care).

#### 3.2 Study population:

The study population will be patients with confirmed AF on an electrocardiogram presenting to Westmead Hospital for clinical care. This includes both inpatients and outpatients.

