### 1.1 Primary objective

To examine, in a randomised controlled trial of 200 hospital inpatients and outpatients with AF, the impact of continued exposure to clinician-created educational videos on AF knowledge at 90 day follow up.

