#### 1.5 Subgroups

The interaction of treatment effect and age, gender, education, ethnicity, subtype of AF and category of presentation will be explored but the study is not powered for these subgroups.

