#### **Primary outcome analysis:**

The primary outcome will be analysed utilising an analysis covariance (ANCOVA), with age, gender, education and subtype of AF incorporated as covariates. Where baseline data are available, this will also be incorporated into the model as a covariate. An unadjusted two-tailed t-test will also be performed. We will report p-values and 95% confidence intervals.

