## 5 Secondary outcome analysis

### 5.1 Satisfaction with clinic experience, motivation to maintain medication adherence and medication adherence – outcome determination

Satisfaction with clinic experience will be determined by a score of  $\geq 6$  on a 7-point Likert scale. The proportion of participants achieving this outcome will be compared between intervention and control groups.

Motivation to maintain medication adherence will be determined by a score of  $\geq 6$  on a 7-point Likert scale. The proportion of participants achieving this outcome will be compared between intervention and control groups.

Medication adherence will be determined by responses to the following questions (previously validated for patients with coronary artery disease and utilised in large scale studies of patients with AF):

- 4) **Specific to your atrial fibrillation medication, in the past month, how often did you take your medications as the doctor prescribed?**
  - a. All of the time (100%)
  - b. Nearly all of the time (90%)
  - c. Most of the time (75%)
  - d. About half the time (50%)
  - e. Less than half the time (<50%)
  - f. No atrial fibrillation medication
- 5) **Specific to your atrial fibrillation medication, in the past month, how often did you forget to take one or more of your prescribed medications?**
  - a. Never
  - b. Once
  - c. 2-3 times
  - d. Once per week
  - e. Several times per week
  - f. Nearly every day
  - g. No atrial fibrillation medication
- 6) **Specific to your atrial fibrillation medication, in the past month, how often did you decide to skip one or more of your prescribed medications**

- a. Never
- b. Once
- c. 2-3 times
- d. Once per week
- e. Several times per week
- f. Nearly every day
- g. No atrial fibrillation medication

Non-adherence will be defined as per previous studies:

- 7. Response to question 1 of “Most of the time (75%) or less OR
- 8. Response to question 2 of “once per week” or more OR
- 9. Response to question 3 of “once per week” or more OR

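### Inpatients and outpatients are pooled, but setting is not a pre-specified covariate in any main model

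*Combined protocol and SAP*

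**What the plan says.** **Population.** Protocol 3.2 and SAP section 2 admit both settings: "This includes both inpatients and outpatients". The SAP's primary objective (1.1) says the same: "To examine, in a randomised controlled trial of 200 hospital inpatients and outpatients with AF".

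**How the settings differ.**
- Recruitment (Protocol 3.3): outpatients are found from cardiology clinic lists and telephoned. Inpatients are approached only after referral by the treating doctor, and only when the hospital's COVID-19 policy allows it.
- Usual care (Protocol section 4): posters, pamphlets and a television in the waiting room, against variable ward care that may include teaching on rounds.
- First follow-up survey (Protocol section 6): end of clinic for outpatients, within 2 days for inpatients.

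**Randomisation.** Protocol 3.4 specifies 1:1 permuted blocks of 4 and 2 and names no stratification factor.

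**Primary model.** SAP 3.1 specifies an ANCOVA "with age, gender, education and subtype of AF incorporated as covariates", plus the baseline value where available. SAP 4.1.1 repeats the four covariates. Protocol section 7 and SAP 1.6 list baseline JAFKQ and education level.

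**Secondary models.** SAP 3.1 and 5.1.1 use age, gender, education and AF subtype; 3.1 also adds the baseline value where there is one. Protocol section 7 and SAP 1.6 instead adjust for number of medications and for total time in clinic, the latter marked as being for outpatients.

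**Related provisions.** SAP 1.5: "The interaction of treatment effect and age, gender, education, ethnicity, subtype of AF and category of presentation will be explored", with the statement that the study is not powered for this. SAP 3.1 adds further regression if baseline risk factors differ significantly between arms. Setting is not a row in the SAP baseline tables (eTables 5 to 8).

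**Satisfaction.** Most sections call the endpoint satisfaction with clinical care. SAP 5.1 changes the label: "Satisfaction with clinic experience will be determined by a score of" at least 6 of 7.

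**The concern.** Setting is known for every patient at enrolment and could plausibly predict knowledge, satisfaction and adherence. When a prognostic factor is neither balanced by design nor adjusted for, its contribution stays in the residual variance, and any chance imbalance between arms moves the estimate.

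The two related provisions do not fill the gap. The interaction in SAP 1.5 is exploratory and does not adjust the main estimate. Its term is undefined, so reading it as inpatient versus outpatient is an inference. The rule in SAP 3.1 is triggered by a significance test, does not name setting, and yields an additional analysis, not the main one. Because setting is not tabulated, the plan does not show that an imbalance would be noticed.

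Satisfaction is the most exposed outcome. It is measured once, after the intervention, at a time point that depends on setting, and it has no baseline value to absorb differences between settings.

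**Working it through.** **Inputs from the documents** (Protocol section 7, SAP 1.6): 100 per arm, 15% attrition (85 per arm analysed), SD 18, two-sided 5%, 90% power, target difference 8.95 points.

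**Assumed inputs.** The documents give neither the inpatient share q nor the difference d in mean JAFKQ between settings. I take q = 10% to 50% and d = 5 to 10 points.

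**1. The plan's own figure.** SE = 18 × √(2/85) = 2.76. Power = Φ(8.95/2.76 − 1.96) = 0.900, so the stated 90% reproduces. With the t distribution, power is 89.7% and the difference detectable with 90% power is 9.00 points.

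**2. Adding setting as a covariate.** Variance explained: R² = q(1−q)d²/18². Residual SD = 18 × √(1−R²). Power is t-based with 85 per arm. The last column is the 95% limit of the shift in the unadjusted estimate from chance imbalance, d × 1.96 × √(q(1−q) × 2/85).

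| q | d | R² | Residual SD | Power | Detectable difference | Shift (± points) |
|---|---|---|---|---|---|---|
| 10% | 5 | 0.7% | 17.94 | 89.9% | 8.97 | 0.45 |
| 10% | 10 | 2.8% | 17.75 | 90.5% | 8.88 | 0.90 |
| 25% | 5 | 1.4% | 17.87 | 90.1% | 8.94 | 0.65 |
| 25% | 10 | 5.8% | 17.47 | 91.3% | 8.74 | 1.30 |
| 50% | 5 | 1.9% | 17.83 | 90.2% | 8.91 | 0.75 |
| 50% | 10 | 7.7% | 17.29 | 91.9% | 8.65 | 1.50 |

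The gain in power is 89.9 − 89.7 = 0.2 to 91.9 − 89.7 = 2.2 percentage points. The imbalance in inpatient share behind the last column is ±9.0, ±13.0 and ±15.0 percentage points for q = 10%, 25% and 50%. The largest shift, 1.5 points, is 1.5/2.76 = 0.54 of one SE.

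**3. Type I error.** In 20,000 simulated null trials per case (d = 10, simple randomisation, unadjusted t-test), the rejection rate was 0.051 at q = 25% and 0.050 at q = 50%. Pooling does not inflate it.

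**4. What the significance trigger would miss.** With 100 per arm at baseline, a difference in inpatient share reaches p < 0.05 at about 1.96 × √(q(1−q) × 2/100). This is 8.3 percentage points at q = 10% and 13.9 at q = 50%. Smaller imbalances would lead to no adjustment.

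**5. What the interaction can show.** SE = 18 × √(2/(85q) + 2/(85(1−q))) = 9.2, 6.4 and 5.5 for q = 10%, 25% and 50%. Power for an interaction as large as 8.95 points is 16%, 29% and 37%.

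**6. Satisfaction.** Assume a 20-point difference between settings in the proportion satisfied. Multiplying by the ±9.0 to ±15.0 point imbalance gives a shift of up to ±1.8 to ±3.0 percentage points. At the planning values of 60.0% and 82.2% with 85 per arm, SE = √(0.600 × 0.400/85 + 0.822 × 0.178/85) = 6.7 percentage points. This too is less than half an SE, but no baseline measure exists to reduce it.

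**7. The outpatient-only covariate.** Total time in clinic has no value for an inpatient, and no rule says how inpatients enter that model. If they were dropped as missing, the adjusted result would exclude randomised patients, whereas SAP 3.1 says that analyses will include all of them.

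**The case against.** The other side has a good deal of ground, and most of it stands.

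- Randomisation protects the pooled comparison. Differences in usual care and survey timing affect both arms, and chance imbalance is already reflected in the confidence interval. Not stratifying a 200-patient trial by setting is a legitimate choice.
- The effect on the primary outcome is small. The 1.5-point shift needs half the patients to be inpatients, a 10-point difference between settings and an extreme imbalance, all at once. Inpatient recruitment is conditional, so a 50% share has no support in the documents. Small blocks may limit imbalance further.
- Baseline JAFKQ, and baseline adherence and motivation under SAP 3.1, would absorb part of any stable difference between settings.

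A reader might go further and infer that the trial was written for clinic attenders, since the specific aim asks "whether a series of clinician-designed educational videos delivered prior to clinic improves" and the hypothesis refers to "educational videos prior to and post clinic appointment will higher knowledge of AF". The documents do not support that. The protocol's primary objective does not mention clinic, and the SAP objective names both settings.

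A reader might also infer that the satisfaction question does not apply to inpatients. That does not follow either. The endpoint is nearly always called satisfaction with clinical care, inpatients have their own time point, and the item text is not shown. Only SAP 5.1 and 5.1.1 use the clinic label. Limiting the endpoint to outpatients would remove randomised patients and an inpatient assessment that the protocol plans.

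The objection does not show that setting is already in a main model. It is not.

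**Conclusion.** The point holds as a modest weakness in the analysis plan. Setting is absent from every listed covariate set, and the two related provisions do not put it there. The consequence is lost precision and less protection against chance imbalance. The stated sample size reproduces and need not change, and type I error is not affected.

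For the primary outcome, adjustment is worth about 0.2 to 2.2 percentage points of power under the assumed ranges, and less once baseline JAFKQ is in the model. For satisfaction, the case rests on the missing baseline measure and the setting-dependent timing more than on a large number. All these sizes depend on an assumed inpatient share and assumed differences between settings.

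The change is worth making because it costs almost nothing. The conflict between the secondary covariate lists does not depend on any assumed figure and needs resolving in any case.

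**What to change.** 1. In SAP 1.5, define category of presentation as inpatient or outpatient at enrolment, and add it as a row in the baseline tables.
2. Add it as a fixed covariate to the primary ANCOVA (SAP 3.1 and 4.1.1) and to the log-binomial and robust Poisson models (SAP 3.1 and 5.1.1). Align Protocol section 7 and SAP 1.6 with this.
3. Keep all randomised patients in the satisfaction analysis. Call the endpoint satisfaction with clinical care throughout, including SAP 5.1 and 5.1.1, and also report it by setting.
4. Settle on one covariate list for the secondary outcomes. If total time in clinic is kept, state how inpatients are handled or confine it to a labelled outpatient analysis.

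The cost is one more model parameter, a variable already known for every patient, and some rewording. If the extra term stops the log-binomial model converging, SAP 3.1 already provides the robust Poisson fallback. The sample size stays as it is, and no change to the randomisation is needed.

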#### 3.3 Eligibility and recruitment

##### Inclusion

1. Adults aged 18 years and over
2. Atrial fibrillation or atrial flutter diagnosed on electrocardiogram
3.  $CHA_2DS_2VASc > 0$  and/or currently prescribed anticoagulation therapy
4. Have an email address or active mobile number

##### Exclusion

1. Too unwell (physically or mentally) to participate in surveys

2. Previously allocated to either condition of the study
3. Insufficient English to understand video content or to participate in the audit surveys

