## **Recruitment**

### *Outpatient clinics*

Eligible patients will be recruited prior to their physical or telehealth outpatient appointment by trained research staff. Staff will screen clinic lists for all outpatient cardiology clinics and identify patients that meet study inclusion criteria.

These patients will be contacted via telephone by study staff and, if agreeable, will be emailed a link. This link will take participants directly to a study description document, followed by baseline surveys and, depending on intervention allocation, either a message thanking them for their participation or the intervention videos.

If patients are physically attending the hospital for their appointment, they will be offered the study intervention on a study iPad in the clinic waiting room or have the option to participate in the study via their own device prior to the appointment.

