### **Intervention:**

Patients randomised to the intervention arm will view the study description document and complete baseline surveys. Following this, they will be automatically delivered the series of 4 clinician-developed videos.

Intervention participants will then either receive a link to the intervention videos once/week via text/email.

Reviewers can view the video series at the following link:

<https://vimeo.com/showcase/7683573>

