Following informed consent, patients completed the audiovisual educational module during the otherwise non-utilized waiting time prior to their consultation for AF. Patients accessed the web-based module through either the URL or QR Code generated by REDCap. This was done using either the single Apple iPad that was already owned by the specialist clinic, or mobile smart devices that the patients already owned.

The intervention was then further enhanced by DM and AT utilizing VideoScribe® technology to increase the acceptability of video content.

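### The exclusion for earlier participation does not cover people who saw the videos in the pilot evaluation, and the planned baseline data would not identify them

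*Combined protocol and SAP*

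**What the plan says.** Protocol 3.3 lists three exclusions. The second is the only one about earlier participation: "Previously allocated to either condition of the study". The exclusion list under SAP section 2 repeats it without a wider rule.

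Protocol section 2 reports a pilot: "The intervention has been evaluated in an observational, non-randomised study of 104 patients with AF". Protocol 4.1 describes how the module was used: "patients completed the audiovisual educational module during the otherwise non-utilized waiting time prior to their consultation for AF", either on "the single Apple iPad that was already owned by the specialist clinic" or on the patients' own devices. The satisfaction and visual analogue scales described in 4.1 match the results given in section 2, so I read both as the same evaluation. Section 4.1 adds that the videos were afterwards reworked with animation "technology to increase the acceptability of video content".

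Protocol 1.1 calls the programme "an AF educational program developed by staff at Westmead Hospital". The trial recruits at the same hospital, and for outpatients: "Staff will screen clinic lists for all outpatient cardiology clinics and identify patients that meet study inclusion criteria". Under Protocol section 4, intervention participants see the four videos after the baseline surveys and then "receive a link to the intervention videos once/week via text/email". Control participants have usual care.

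The baseline items in Protocol section 5 cover demographics, AF subtype, medical history and medications. Prior viewing of the videos is not among them.

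**The concern.** The second exclusion is there to stop someone entering the comparison twice, but it is worded around allocation and not around exposure. A non-randomised evaluation allocates nobody, so its participants pass the criterion as written. One of them could be assigned to usual care having already seen material on the same subject. Another could be assigned to the videos with some of the gain already in the baseline score. In both cases the difference that person can contribute at 90 days may be smaller than the one the trial was sized for.

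The second part of the concern is that the gap cannot be closed afterwards. If prior viewing is not asked about at screening or baseline, the planned data give no way to count these participants or to repeat the analysis without them.

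**Working it through.** **Inputs.** Protocol section 7 and SAP 1.6 give 200 participants (100 per arm), 15% attrition, SD 18, two-sided 5% and a difference of 8.95 points with 90% power. Protocol section 2 gives 104 pilot patients. Two quantities are not in the documents and are assumed: *f*, the share of each arm that saw the pilot videos, and *c*, the share of the full contrast that prior viewers still show (0 is the worst case).

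**Step 1: reproduce the plan's figure.**
- Evaluable per arm: 100 × (1 − 0.15) = 85.
- Standard error of the difference: 18 × √(2/85) = 2.761.
- Detectable difference, normal approximation: (1.960 + 1.282) × 2.761 = 8.95. This agrees with the plan.
- Power for 8.95 points: 90.0% by the normal approximation and 89.7% by the noncentral t (168 degrees of freedom). The planned comparison is a t-test, so 89.7% is the reference below.

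**Step 2: dilute the difference.** Prior viewers are randomised 1:1 like everyone else, so the expected share is the same in both arms. Holding the SD at 18, the expected difference is 8.95 × [1 − *f* × (1 − *c*)].

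| Overlap *f* | Prior viewers in 200 | Difference, *c* = 0 | t-test power | Difference, *c* = 0.5 | t-test power |
|---|---|---|---|---|---|
| 0% | 0 | 8.95 | 89.7% | 8.95 | 89.7% |
| 5% | 10 | 8.50 | 86.5% | 8.73 | 88.1% |
| 10% | 20 | 8.055 | 82.7% | 8.50 | 86.5% |
| 20% | 40 | 7.16 | 73.2% | 8.055 | 82.7% |

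For example, at 10% and *c* = 0 the difference is 8.95 × 0.90 = 8.055, the noncentrality is 8.055/2.761 = 2.917, and power is 82.7%. At 20% and *c* = 0.5 the factor is 1 − 0.20 × 0.5 = 0.90, which gives the same result.

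**Step 3: what baseline adjustment does.** Knowledge retained from the pilot would appear in the baseline JAFKQ score, so a model with that covariate absorbs part of the problem. Protocol section 7 includes baseline JAFKQ in the ANCOVA. SAP 3.1 includes it where available. The covariates listed in SAP 4.1.1 do not include it, and the t-test is unadjusted. The documents give no correlation between baseline and 90-day scores, so this relief cannot be quantified from them. Nor does adjustment restore a contrast that is smaller in people who have already seen the material.

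**The case against.** The strongest objection is that overlap is inferred. The pilot clinic is called only a specialist clinic, and no section says it is one of those screened for the trial. A pilot patient would also have to attend during recruitment, meet the inclusion criteria and consent. This stands. A reader might note that 104 is over half of 200 and infer a large overlap, but that compares a past cohort with a target sample and estimates nothing.

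A second objection is that the pilot was one sitting with a version later enhanced, whereas the trial tests continued exposure (SAP 1.1) with weekly links. This also stands. A reader might infer that the trial intervention itself is carried into the control arm, or that prior viewers can show no contrast at all. The documents do not support either inference. A prior viewer in the intervention arm still receives the enhanced videos and the links, and one in control does not. Zero further contrast is therefore only a worst case, which is why the half-contrast figures are shown beside it.

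A reader might also infer that the engagement groups are blurred. They are not: SAP 5.1.2 counts viewing during the intervention period, so pilot viewing does not enter.

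None of this alters the wording of the exclusion or supplies the missing baseline item.

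**Conclusion.** The gap in eligibility is real and its size is unknown. As written, pilot viewers who otherwise qualify can be randomised to either arm, and the planned baseline data would not show who they are. Shared hospital origins make some overlap plausible but do not establish it.

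If overlap occurs, the expected consequence is dilution towards no difference and some loss of power, partly offset where baseline JAFKQ is a covariate. It would not favour the videos, so a positive result would not be undermined by it. A null or borderline result would be harder to interpret.

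The loss is small at 5% overlap (1.6 to 3.2 percentage points of power) and matters at 20% (7.0 to 16.5 points), each range running from half the contrast to none. These figures rest on the assumed overlap and retained contrast, an SD held at 18, and equal expected shares of prior viewers in the two arms. The plan's power calculation reproduces and needs no correction.

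**What to change.** In Protocol 3.3 and in the SAP's exclusion list, let the second exclusion read "Previously allocated to either condition of the study", followed by: or previously viewed the AF educational video module, including in the earlier observational evaluation. Check it with one question at screening. If identifiable pilot records exist, check against those too; the documents do not say that they do, and the fix does not depend on them.

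If the sponsor prefers to keep these patients, add prior viewing to the baseline items in Protocol section 5, and add to SAP 3.2 a sensitivity analysis of the primary outcome without prior viewers.

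The cost is one extra screening question and, under exclusion, the loss of probably a few otherwise eligible patients. The sample size does not change.
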